## Methods and analysis

This RCT protocol follows the Standard Protocol Items for Randomized Trials (SPIRIT) statement guidelines [18] and all methods were carried out with relevant guidelines and regulations. The trial is registered in the ISRCTN registry (ISRCTN16185698). Supplementary files include the SPIRIT chart (S1), SPIRIT checklist (S2), and WHO Trial Registration Data Set (S3).

### Study design and setting

This is a pragmatic, multicentre RCT that will investigate whether group-delivered CBT-I, compared with a waiting list, reduces insomnia severity. The group-delivered CBT-I will be offered at the public, interdisciplinary primary care Healthy Life Centres in Norway. The group-delivered CBT-I investigated in this study is an existing treatment option at the Healthy Life Centres for adults with insomnia symptoms. A flow chart of the planned study design of the RCT is shown in Fig. 1.

**Fig. 1 Fig1:**
[figure not shown]
Planned study design of the pragmatic, multicentre randomized controlled trial investigating the effectiveness of group-delivered CBT-I on insomnia severity in primary care. ISI = Insomnia Severity Index, CBT-I = cognitive behavioural therapy for insomnia

### Participants

#### Recruitment

Recruitment of centres lasted from April 2022 to September 2022. Of the 280 Healthy Life Centres in Norway, 49 offer the group-delivered CBT-I treatment. All 49 centres were contacted via e-mail with information about the research project. Of the 49 centres, 26 have agreed to participate in the research project (53% response rate).

Recruitment of participants with insomnia commenced in August 2022. Participants are recruited using advertisements in newspapers and news websites, social media, webpages for the involved municipalities and Norwegian University of Science and Technology (NTNU), through the Healthy Life Centres, and poster advertisements in waiting rooms of general practitioners and physiotherapists. Healthcare personnel will be informed about the RCT using relevant communication channels and may refer patients to the group-delivered CBT-I treatment.

#### Eligibility and procedure

All adults interested in participation will enter a secure online screening portal, through a link on the project’s webpage. The screening portal includes a series of self-rating questions pertaining to the eligibility criteria. Inclusion criteria include age ≥ 18 and Insomnia Severity Index (ISI) score ≥ 12, indicating insomnia symptoms with a significant impact on the individual [19]. Since this is a pragmatic trial, we will only exclude adults with diagnosed major psychiatric, somatic, or neurological disorders for which CBT-I may be contraindicated (see Fig. 1). All potential participants will have to confirm their proficiency in the Norwegian language.

The researchers will evaluate inclusion criteria of each potential participant. Eligible participants will be sent a digital consent form. After consenting, participants will be randomized, and thereafter informed of allocation outcome. Participants in the treatment group will be contacted by the respective Healthy Life Centre employees about the next available treatment group. If they cannot participate (i.e., the time or location of treatment group does not align with participants’ schedule), they will be excluded. All participants will obtain invitations to complete questionnaire batteries and sleep diaries via e-mail at four measurement timepoints (see Fig. 1). Non-responders will receive reminders via SMS or phone call. Those who still do not respond will be followed up by phone and asked instead to report only on the primary outcome measure (ISI).

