#### Randomization

Participants will be randomized to the intervention and control group according to a 2:1 ratio. Thus, groups will be formed quicker with more intervention participants, allowing more CBT-I groups to be formed during the limited timeframe of the trial. Unequal randomization may also facilitate recruitment, as participants may be more likely to enrol if they perceive their chance of receiving the intervention to be greater than being placed on the waiting list. Many participants seek out the treatment themselves and reducing the number of waiting list participants is also desirable for ethical purposes. Finally, more intervention group participants will ensure the conduct of planned moderation and exploratory mediation analyses with increased power. Unequal randomization in similar research has previously been recommended [20–22].

Randomization will be performed by the project leader in a secure digital platform for multicentre clinical studies, eForsk. eForsk is a standalone data management system used for electronic self-report data, developed by the Central Norway Regional Health Authority IT department. The randomization will be based on a computerized allocation sequence stratified on each of the participating centres. This will be generated by a third party, the Clinical Research Unit at the Faculty of Medicine and Health Sciences at NTNU. The project leader will be blinded for the block sizes and the allocation sequence. The project leader and research team will thus not influence the randomization process in any way. An overview of the allocation sequence can be provided by the Clinical Research Unit upon request. Participants and the Healthy Life Centre employees will not be masked to the participants’ group assignment.

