#### Control group

Participants in the control group will be placed on a waiting list for 6 months. They will not be restricted from seeking other forms of treatment during the waiting period, nor from using sleep medications. After the waiting period, they will have the possibility to participate in the treatment at their Healthy Life Centre, which will be offered to them by a Healthy Life Centre employee during the waiting period.

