#### Statistical analysis plan

A detailed statistical analysis plan will be published before unblinding of study data. Descriptive statistics will be presented stratified by group allocation. Categorical and binary variables will be summarized as counts and percentages, while continuous variables as means and standard deviations or medians and interquartile range, as appropriate.

The primary outcome will be analyzed using the intention-to-treat principle. Linear mixed models will be used to estimate the mean differences between T1 and T3 in ISI with 95% confidence intervals between the two groups. For continuous secondary outcomes, linear mixed models will be utilized, while binary secondary outcomes (e.g., clinically relevant change in ISI) will be analyzed using logistic mixed models. Models will include time, group, time–group interaction and baseline covariates. Since we expect that some intervention group participants will miss some treatment sessions, per-protocol analyses will be used for individuals who complete ≥ 3 sessions. Missingness patterns will be investigated, and pattern-mixture models will be used to simulate situations where the data are not missing at random. Interim analyses will not be carried out, due to limited expected adverse effects of the treatment, and because all intervention group participants are followed up by the Healthy Life Centre employees during the treatment.

Moderation analyses will be conducted to investigate whether demographics (e.g., age, sex) chronotype, treatment group size, physical activity, length of prior insomnia treatment, and duration of insomnia moderate the effectiveness of group-delivered CBT-I on primary and secondary outcomes. Exploratory mediation analyses will be conducted to investigate mechanisms of change in the primary and secondary outcomes, focusing on psychological measures of beliefs about sleep, reactivity to stress, and sleep-related self-efficacy.

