### Monitoring

The time and effort necessary for the self-reported assessments may impose some participant burden. To increase compliance and alleviate participant burden, control group participants will be offered a monetary compensation of 150 NOK (10 NOK ~ 1 EUR) if they report on all questionnaires and ≥ 4 sleep diaries at timepoints T1, T2, T3 and T4, respectively. Moreover, participation in the group-delivered CBT-I is typically subject to a fee (varying from 200–550 NOK between the Healthy Life Centres), but intervention group participants will be exempted from paying this fee.

The study will impose participant focus on insomnia, own sleep, and health-related consequences. For some, this may be perceived as stressful or worrying. However, all participants are seeking out insomnia treatment, and most likely already have an increased focus on these aspects in their daily lives. The harm associated with participation is therefore deemed acceptable. Participants who contact the research team or the Healthy Life centre employees about participation burden will be followed-up individually. All participants will be informed about the possibility to terminate participation in the study for any reason.

Control group participants are placed on a 6-month waiting list before they can participate in the treatment. This waiting time is deemed acceptable, as the usual waiting time for the treatment varies from 1 to 6 months, depending on the centre (i.e., centres in more sparsely populated municipalities have longer waiting periods, as they organize fewer treatment groups). Likewise, some intervention group participants may experience a waiting time of up to 6 months before they can begin treatment. This reflects natural capacity limitations. To alleviate the waiting time, multiple centres will be organizing more frequent treatment groups, and waiting times over 3 months for the intervention group participants will rarely occur. Relevant for all study participants is the notion that participation in the RCT will not be a prerequisite for attending the group-delivered CBT-I treatment at the Healthy Life Centers – those who decline to take part in the RCT will still be able to attend the treatment.

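### Treatment-group participants who cannot make the offered group are excluded after randomisation with no matching rule for controls, which on the plain reading conflicts with the promised intention-to-treat analysis

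*Protocol article*

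**What the plan says.** The order of events is in the protocol article, section Eligibility and procedure. First: "After consenting, participants will be randomized, and thereafter informed of allocation outcome". Next: "Participants in the treatment group will be contacted by the respective Healthy Life Centre employees about the next available treatment group". Then: "If they cannot participate (i.e., the time or location of treatment group does not align with participants’ schedule), they will be excluded". The sentence after that says that all participants are invited to the questionnaires and sleep diaries at four timepoints.

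For the other arm, the section Control group says: "Participants in the control group will be placed on a waiting list for 6 months". Controls are offered the treatment by a centre employee during the wait, for use afterwards. No exclusion is attached to their answer.

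The section Statistical analysis plan says: "The primary outcome will be analyzed using the intention-to-treat principle". It adds, for missed sessions, that "per-protocol analyses will be used for individuals who complete ≥ 3 sessions".

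Three other places bear on the point:

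- Randomization: "Participants and the Healthy Life Centre employees will not be masked to the participants’ group assignment".
- Data management and auditing: the centre records when treatment starts, and the researchers time the questionnaires from that date.
- Monitoring: "some intervention group participants may experience a waiting time of up to 6 months before they can begin treatment".

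**The concern.** Randomisation makes the arms comparable as long as everyone randomised is followed and analysed. Here a filter is applied afterwards, in one arm, by people who know the allocation. It depends on whether the participant can fit a particular group. The controls who would have failed the same check are not identified and remain in.

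If ability to attend is related to how insomnia develops without treatment, the remaining treatment group differs in prognosis from the full control group. The primary ISI comparison at 3 months then mixes treatment effect with selection. The target also shifts, from the effect of offering the service to the effect among people who could take up the offer. That matters for a trial presented as pragmatic.

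An analysis plan cannot fully put this right later. If excluded people are not sent the questionnaires, their outcomes are never collected.

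**Working it through.** **The passages side by side**

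| Step | Treatment group | Control group |
|---|---|---|
| Consent, randomisation, allocation disclosed | yes | yes |
| Contact about fit with the next group | yes, after allocation | none that affects trial status |
| Consequence of not fitting | excluded | no rule stated |
| Promised primary analysis | intention to treat | intention to treat |

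If excluded means removed from the trial, rows 3 and 4 cannot both hold. The rule also sits badly with the preceding paragraph of the same section, which limits exclusions to certain diagnosed disorders.

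**Inputs for an illustration of size**

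- From Sample size: 194 intervention and 98 control participants, 30% attrition, planned effect d = 0.50.
- Not in the document, so assumed: the share e of the intervention arm excluded, 5–20% (194 × e is about 10 to 39 people); and the difference D in untreated outcome between excludable and other participants, 0.2–0.5 SD, with excludable people doing worse.

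The plan gives no figure for these exclusions, so there is none to reproduce. Its total of 192 for d = 0.50 at 90% power does reproduce (64 + 128, power 90.1%), but the point does not depend on it.

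**Formulas**

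Let δ be the effect in people who can attend, and suppose that excludable people gain nothing.

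- Effect of the offer in everyone randomised: (1 − e)δ.
- Expected estimate after one-arm exclusion: δ + eD. The controls still contain the fraction e with the worse outcome; the treatment group does not.
- With D = 0, overstatement of the offer effect: δ / [(1 − e)δ] − 1 = e / (1 − e).
- Bias in δ itself from prognosis: eD.

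**Results**

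| e | Intervention participants left (of 194) | Ratio to 98 controls | e/(1 − e) | eD, D = 0.2 to 0.5 | Two-sided rejection rate with no true effect |
|---|---|---|---|---|---|
| 5% | 184 | 1.88 | 5.3% | 0.010–0.025 SD | 5.1–5.3% |
| 10% | 175 | 1.78 | 11.1% | 0.02–0.05 SD | 5.2–6.3% |
| 20% | 155 | 1.58 | 25.0% | 0.04–0.10 SD | 5.8–9.9% |

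The last column uses a noncentral t with noncentrality eD × √[n₁n₂/(n₁ + n₂)], where n₁ = 98 × 0.7 = 68.6 and n₂ = 194 × (1 − e) × 0.7. For e = 20% and D = 0.5, n₂ = 108.6 and the noncentrality is 0.10 × √42.05 = 0.65, which gives 9.9%.

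Against d = 0.50, a bias of 0.01–0.10 SD is 2–20% of the planned effect (0.01/0.50 to 0.10/0.50). Precision is hardly touched: power at d = 0.50 after 30% attrition falls from 92% to 91%, 91% and 90%. The issue is bias, not sample size.

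**The case against.** The strongest objection concerns the word itself. The next sentence invites all participants to the questionnaires, and the analysis section commits to intention to treat. Read together, *excluded* could mean only that the person does not join the treatment group. Fig. 1, which might settle it, is not available in the text reviewed. A reader might infer that the protocol certainly drops these people from the analysis; the text does not establish that. Trial-level exclusion is still the likelier reading. The paragraph before uses the same verb for trial eligibility. Someone who cannot attend is already untreated, so a treatment-only exclusion would add nothing. Questionnaires are timed from a treatment start date that such a person does not have. No sentence keeps them in follow-up or in the analysis set.

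Other parts of the objection stand:

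- **Size.** Both the exclusion rate and the prognosis difference are assumed. The 5–25% figure is a gap between two targets, the offer and attendance, not bias in the effect among attenders. The direction of the prognostic bias is also unknown.
- **Who is excluded.** The article names only time and location. It does not say that groups meet in the daytime, or that less motivated people would be removed.
- **Adjustment.** The models include baseline covariates, and shift work, occupation and children in the household are recorded. Adjustment could remove part of an imbalance, though not what is unmeasured. It would be too strong to say that the mixed model can do nothing.
- **Per-protocol analysis.** One might infer that selecting people with at least 3 sessions is a second error. It is offered as a supplement to an intention-to-treat primary analysis and contradicts nothing. How controls enter it can be left to the detailed analysis plan.

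**Conclusion.** The concern holds as a conflict between the section Eligibility and procedure and the section Statistical analysis plan, which must be reconciled. On the plain reading, the protocol prescribes a one-arm exclusion after randomisation and disclosure of allocation. That is incompatible with intention to treat and can bias the primary comparison if ability to attend is prognostic. On the lenient reading there is no bias from this source, but the article does not state that reading.

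The document does not allow the size to be derived. With an assumed 5–20% excluded, the effect of the offer is overstated by about 5–25% if they would gain nothing. An assumed prognosis difference of 0.2–0.5 SD gives a bias of about 0.01–0.10 SD. At the lower end this is negligible. At the upper end it is a fifth of the planned effect, and the false-positive rate nearly doubles. A claim that the trial's result is already invalid would go beyond the document, because the number excluded and what happened to their follow-up are not reported.

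**What to change.** Replace the exclusion sentence. It should say that participants who cannot attend the offered group stay in the trial, are invited to the T2–T4 assessments (at least the ISI), and are analysed in the arm to which they were randomised. Report their number as non-starters.

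Give them a substitute anchor date, such as the start date of the group they were offered, because questionnaires are otherwise timed from treatment initiation. For people already excluded since recruitment opened in August 2022, resume the remaining assessments where consent allows. Those already missed cannot be recovered.

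Where group times are known in advance, availability may also be asked in the screening portal before randomisation, for both arms. This narrows the population to people able to attend and should be stated as such. With waits of up to 6 months, group times will not always be known at screening, so this cannot replace the retention rule. A complier-average analysis may be added as a supplement; the planned per-protocol analysis need not be removed.

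The cost is a somewhat smaller intention-to-treat effect and a little more follow-up work. If those retained gain no benefit, d = 0.50 becomes 0.50 × (1 − e) = 0.475, 0.45 or 0.40 at e = 5%, 10% or 20%. With 98 and 194 randomised and 30% attrition, power is then 89%, 86% or 77%, against 92% with no such cases. That reduction is the real effect of offering the service, which exclusion would hide.

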#### Randomization

Participants will be randomized to the intervention and control group according to a 2:1 ratio. Thus, groups will be formed quicker with more intervention participants, allowing more CBT-I groups to be formed during the limited timeframe of the trial. Unequal randomization may also facilitate recruitment, as participants may be more likely to enrol if they perceive their chance of receiving the intervention to be greater than being placed on the waiting list. Many participants seek out the treatment themselves and reducing the number of waiting list participants is also desirable for ethical purposes. Finally, more intervention group participants will ensure the conduct of planned moderation and exploratory mediation analyses with increased power. Unequal randomization in similar research has previously been recommended [20–22].

Randomization will be performed by the project leader in a secure digital platform for multicentre clinical studies, eForsk. eForsk is a standalone data management system used for electronic self-report data, developed by the Central Norway Regional Health Authority IT department. The randomization will be based on a computerized allocation sequence stratified on each of the participating centres. This will be generated by a third party, the Clinical Research Unit at the Faculty of Medicine and Health Sciences at NTNU. The project leader will be blinded for the block sizes and the allocation sequence. The project leader and research team will thus not influence the randomization process in any way. An overview of the allocation sequence can be provided by the Clinical Research Unit upon request. Participants and the Healthy Life Centre employees will not be masked to the participants’ group assignment.

### Interventions

#### Group-delivered CBT-I

Participants in the intervention arm will be offered a group-delivered CBT-I treatment developed by the Norwegian Health Directorate in collaboration with the Norwegian Competence Centre for Sleep Disorders. The intervention will be provided repeatedly at the 26 centres recruited for this study. Group size varies between centres, from 5 to 15 participants per treatment group. The treatment is a first line, low-threshold service for sleep problems in primary care without the need of referral.

The intervention will follow the standardized CBT-I program, with some adaptations based on input from researchers, clinicians, and experiences of the user group. Components of the intervention are presented in Table 1.

**Table 1 Tab1:** Components of the investigated group-delivered cognitive behavioural therapy for insomnia

Session	Educational components	Group components	Homework
1	Sleep, its functions and sleep/wake regulation Prevalence, symptoms, and consequences of insomnia Using the sleep diary Relaxation technique: Herbert Benson’s relaxation response	Participants meet each other and talk about their experiences with insomnia Participants’ course expectations	Identify three sleep-related habits to target during treatment Fill out sleep diary Fill out Sleep Hygiene Index
2	Sleep hygiene advice Stimulus control Relaxation technique: Progressive muscle relaxation	Participants’ experiences with sleep diary Learning outcomes so far Implemented changes so far	Fill out sleep diary Fill out the Negative Beliefs and Attitudes about Sleep Apply sleep hygiene advice Calculate sleep efficiency in preparation for sleep restriction
3	Dysfunctional beliefs about sleep: Identification and change Principles of sleep restriction	Implemented changes and their effect so far	Fill out sleep diary Fill out an overview of how to challenge own negative thoughts about sleep Apply sleep restriction
4	Management and maintenance of own sleep Motivation for lasting change	Implemented changes and their effect so far Alternatives to dysfunctional beliefs about sleep Adapting the learning outcomes to changing life-circumstances	

The intervention will be conducted by Healthy Life Centres employees who are physiotherapists with extensive experience and knowledge of the treatment. They have participated in a course about delivering the intervention, organized by the Norwegian Health Directorate. All have also participated in an in-person information day, held prior to the start of the RCT, where the research project and the relevant adaptations to the intervention were presented in detail, to ensure a common knowledge basis for all instructors. The meeting was recorded, and distributed to the Healthy Life Centres employees for reference.

